## Abstract

**Background:**

Non-invasive brain stimulation techniques have been widely used in patients with mild cognitive impairment (MCI) to accelerate the recovery of their cognitive functions. However, the clinical efficacy of single non-invasive stimulation techniques in treating MCI still requires further improvement. The combination of two non-invasive neuromodulation techniques can enhance the synergistic effects of the treatment. Repetitive transcranial magnetic stimulation (rTMS) regulates the cortical-subcortical network in a “top-down” manner, while transcutaneous auricular vagus nerve stimulation (taVNS) modulates the brainstem-limbic system-cortical pathway in a “bottom-up” fashion. We will combine rTMS and taVNS, anticipating synergistic regulation through dual pathways to achieve multi-level neural remodeling effects and improve MCI.

**Methods:**

This study will investigate the effectiveness of combined rTMS and taVNS therapy in improving the cognitive function of MCI patients. We will enroll 88 participants and randomly assign them to single-stimulation groups and combined-stimulation groups. The single-stimulation groups will be further randomized in a 1:1 ratio into a rTMS + sham taVNS stimulation group and a taVNS + sham rTMS stimulation group; the combined-stimulation groups will be randomized in a 1:1 ratio into an rTMS + taVNS group and an rTMS sham stimulation + taVNS sham stimulation group. All patients will receive treatment for 4 weeks. Assessments will be conducted before treatment (T0), 4-week treatment (T1), and 4-week post-treatment follow-up (T2). The primary outcome measure will be the Chinese version of the Montreal Cognitive Assessment Basic (MoCA-B), while secondary outcome measures will include the Rivermead Behaviour Memory Test (RBMT), the modified Barthel Index (MBI) for activities of daily living, and the latency and amplitude of event-related potential (ERP) P300.

**Discussion:**

This study is a clinical randomized controlled trial, which innovatively combines two non-invasive modulation techniques to improve cognitive function in patients with MCI. This study can validate the clinical efficacy of the combined TMS + taVNS stimulation, providing a theoretical basis for the application of this technology in clinical settings.

## Introduction

Mild cognitive impairment (MCI) is an intermediate state between normal cognitive function and dementia (Mian et al., 2024; van der Veere et al., 2024). It shows varying degrees of impairment in many cognitive areas such as memory, executive function, and language ability (Knopman and Petersen, 2014; Weston et al., 2011). These problems often lead to a decline in patients’ ability to live daily and an increase in psychological problems (Avery et al., 2023), which seriously increases the social and economic burden. Epidemiology has shown that the prevalence of MCI is higher in the elderly population and increases with age. MCI is particularly common in the community (Stephan et al., 2024). Early recognition and intervention are important for delaying the further decline of cognitive function. By using tools such as the Montreal Cognitive Assessment Scale, MCI can be more effectively detected, and personalized management strategies can be provided to patients (Mian et al., 2024). In conclusion, MCI is a complex clinical condition with diverse manifestations and hazards. An in-depth understanding of the clinical features of MCI and its potential risk factors is critical to developing effective interventions and improving patient outcomes.

As a non-invasive brain stimulation technique, transcranial magnetic stimulation (TMS) can improve cognitive function by regulating the excitability of the cerebral cortex. In recent years, TMS has made some progress in improving MCI. Studies have shown that repetitive transcranial magnetic stimulation (rTMS) can significantly improve overall cognitive function and memory in patients with MCI (Jiang et al., 2020). In addition, rTMS improves cognitive function by regulating neurotransmitter balance and promoting synaptic plasticity (Li and Xiao, 2024). Functional magnetic resonance imaging (fMRI) studies have shown that rTMS can alter the functional connectivity of brain regions associated with cognition, such as increasing the functional connectivity of the left dorsolateral prefrontal cortex (DLPFC) with other brain regions (Li et al., 2020). Due to significant variations in the stimulation parameters of rTMS (such as frequency, intensity, stimulation site, etc.) across different studies, the reproducibility of results is poor. In addition, most of the existing studies are focused on short-term interventions, lacking long-term follow-up data to evaluate the sustained effects of rTMS (Cirillo et al., 2023).

Transcutaneous auricular vagal nerve stimulation (taVNS) is an emerging non-invasive vagal nerve stimulation technique (Farmer et al., 2020). In 2000, Ventureyra first proposed the concept of stimulating the vagus nerve via auricular (ear) skin (Ventureyra, 2000). TaVNS can regulate neural activity in the brain by stimulating the auricular branch of the vagus nerve, thereby improving cognitive functions (Miyatsu et al., 2024). TaVNS can significantly enhance short-term memory and immediate recall abilities in healthy adult (Cibulcova et al., 2024). It can improve the duration of attention by modulating indirect physiological markers, such as salivary α-amylase and cortisol concentrations (Luna et al., 2025). By modulating the activity of the autonomic nervous system and central nervous system, taVNS can improve overall cognitive function (Kang et al., 2024). In summary, taVNS, as an emerging neuromodulation technique, holds significant potential in improving cognitive functions.

No previous studies have reported the combined use of rTMS and taVNS for MCI. The rationale for integrating rTMS with taVNS in this study lies in their synergistic modulation of brain networks through dual regulatory pathways to improve cognitive function. High-frequency rTMS enhances DLPFC excitability via long-term potentiation (LTP) mechanisms. As a key hub for cognitive control, DLPFC activation exerts top-down regulation on cognition-related brain regions, thereby improving cognitive performance. Concurrently, taVNS activates Aβ fibers in the auricular branch of the vagus nerve, transmitting signals to the nucleus tractus solitarius (NTS). This initiates neuroplastic effects through both the locus coeruleus-noradrenergic pathway and the limbic system. The combined use of these two modalities aims to amplify the holistic regulatory effects on cognitive networks through a dual-pathway approach, encompassing both “top-down” and “bottom-up” mechanisms.

Electroencephalography (EEG) is an important tool for the early diagnosis of MCI. It can record the brain’s electrical activity in real time, reflecting the neural synchronization and desynchronization mechanisms (McBride et al., 2014). Patients with MCI often exhibit a weakening of the alpha rhythm and an enhancement of the theta rhythm, and these changes are closely associated with cognitive decline (Babiloni et al., 2021). In event-related potentials (ERPs), specific components such as N200 and P300 exhibit delayed occurrence in patients with MCI. Furthermore, MCI patients show prolonged P300 latency and reduced amplitude, indicating a slowing of cognitive processing speed (Kamal et al., 2021). EEG and ERPs provide critical insights into the neurophysiology associated with MCI.

Therefore, we plan to conduct a prospective, randomized controlled clinical trial. We hypothesize that the combination of rTMS and taVNS may produce synergistic effects, further enhancing the improvement in cognitive function. In addition to administering cognitive behavioral assessments, we will incorporate EEG to explore the neurophysiological mechanisms of this combined therapy.

## Methods

### Study design

The study is a prospective, randomized, controlled clinical trial (Figures 1, 2) that has been registered at the Chinese Clinical Trial Registry (ChiCTR2100049851).^1^

**FIGURE 1 F1:**
[figure not shown]
Schedule of enrollment, interventions and assessments. rTMS, repetitive transcranial magnetic stimulation; taVNS, transcutaneous auricular vagus nerve stimulation; MoCA-B, Montreal Cognitive Assessment Basic; RBMT, The Rivermead Behaviour Memory Test; MBI, modified Barthel Index; ERP-P300, Event-Related Potential P300.

**FIGURE 2 F2:**
[figure not shown]
Study flow diagram. rTMS, repetitive transcranial magnetic stimulation; taVNS, transcutaneous auricular vagus nerve stimulation; MoCA-B, Montreal Cognitive Assessment Basic; RBMT, The Rivermead Behaviour Memory Test; MBI, modified Barthel Index; ERP-P300, Event-Related Potential P300.

### Recruitment of participants

Participants will be recruited from the clinic, inpatient ward, or long-term care facilities near the Department of Rehabilitation, Tongren Hospital, Shanghai Jiao Tong University School of Medicine between January 2025 and December 2025. Residents who meet the inclusion criteria will be recruited.

### Diagnostic criteria

The diagnosis was based on Jak/Bondi’s criteria (Bondi et al., 2014). Participants were diagnosed as MCI if one of the following three criteria was met: (1) he or she had an impaired score, defined as > 1 standard deviation (SD) below the age-corrected normative mean, on both measures within at least one cognitive domain (i.e., memory, language, or speed/executive function); (2) he or she had one impaired score, defined as > 1 SD below the age-corrected normative mean, in each of the three cognitive domains sampled; or (3) he or she had a score on the Functional Assessment Questionnaire (FAQ) = 9 (Gloth et al., 1995) indicating dependence on three or more daily activities.

### Inclusion criteria

(1)Meet the “core” criteria for MCI, as defined by the National Institute on Aging-Alzheimer’s Association workgroups on diagnostic guidelines for Alzheimer’s disease (Albert et al., 2011);(2)Age between 45 and 80 years;(3)Right-handed;(4)A Clinical Dementia Rating (CDR) score of 0.5;(5)Voluntarily agreeing to participate in this study and signing the informed consent form.

### Exclusion criteria

(1)Cognitive dysfunction caused by other reasons (such as medications, vascular conditions, Parkinson’s disease, frontal-temporal lobe degeneration, alcohol dependence, tumors, epilepsy, and hydrocephalus);(2)History of stroke or intracranial space-occupying lesions;(3)Other psychiatric disorders (such as depression or severe affective disorders);(4)Substance abuse, moderate-to-severe hypertension, or systemic diseases (such as acute renal failure or pulmonary infection);(5)Visual or auditory impairments preventing completion of neuropsychological testing;(6)Contraindications to rTMS treatment, such as metallic implants in the body or cardiac pacemakers;(7)Contraindications to taVNS treatment, such as cochlear implants or other implanted electronic devices, conduction block arrhythmias, and asthma;(8)Individuals with skin lesions or infections in the ear area.

### Randomization and allocation

A statistical professional will use MATLAB (version 2020b, MathWorks Inc., Natick, United States) to generate 88 random integers in a randomized sequence. Each patient will be assigned a unique random number based on their enrollment order. The first randomization will divide patients into a combined stimulation group (1–44) and a single stimulation group (45–88) at a 1:1 ratio. Patients in the combined stimulation group will be further randomized at a 1:1 ratio into a real stimulation subgroup (1–22) and a sham stimulation subgroup (23–44). Similarly, patients in the single stimulation group will be randomized into an rTMS + sham taVNS subgroup (45–66) and a taVNS + sham rTMS subgroup (67–88) at a 1:1 ratio. Allocation concealment will be implemented using opaque sealed envelopes. Researchers will open the envelopes sequentially according to enrollment order, and detailed records of the opener and time of unsealing will be maintained.

### Assignment of interventions: blinding

It should be noted that complete blinding of both researchers and participants to the allocation of intervention targets is not feasible due to the inherent visibility of stimulation targets. Therefore, blinding will be selectively implemented, extending exclusively to the assessors and statisticians responsible for data collection and final statistical analyses.

Unblinding of group division will occur in situations where the staff deem this necessary for participant safety.

### Interventions

All participants will receive routine cognitive training.

RTMS will be undergone using a Magventure Rapid stimulator, connected with a figure-of-eight coil (cool-B65) having a 70-mm diameter (MagPro X100, Denmark), generating 6 T as the maximum output. rTMS intensity is set up to a maximum of 90% of the resting motor threshold (RMT) for each participant. Throughout the procedure, subjects will remain in a supine position and will be instructed to remain motionless to ensure precise targeting of the stimulation site. The coil is positioned over the left DLPFC (F3 point according to the EEG 10-20 system). The daily sessions are applied with 1500 rTMS pulses at 10 Hz in short bursts of 50 pulses. In addition, the sham procedure is delivered through the same device with a specially designed coil to create identical noise as real rTMS without any electromagnetic energy. The treatment will be applied once a day for 4 weeks with rest on the weekends (4 weeks of rTMS therapy).

The taVNS device (BC 102-IV, BrainClos, Shenzhen, China) channel will be connected to two silver chloride electrodes (with an outer diameter of 7 mm). Both the anode and cathode of the taVNS will be placed inside the left cavum conchae of the ear, with the cathode positioned medially, 0.5 cm away from the anode. The skin around the left ear will be wiped with alcohol to remove any excess oil and to ensure the best possible conductivity. Stimulation parameters will be adjusted for (1) wave density: 25 Hz; (2) wave width: 500 μs; (3) Intensity: range from 0 to 6 mA in a 30-s on/30-s off cycle, adjusted to the strongest sensation that can be tolerated without pain;(4) duration: 30 min/session, daily, 5 days/week, for 4 weeks. All procedures performed in the sham taVNS group are identical to those in the taVNS group, but the instrument will administer a constant electrical current of 0.5 mA for 30 s. Subsequently, the current intensity is progressively diminished to a null level. If a participant reports no sensation, the researcher will check the device and its connection, reassure the participant of proper device connectivity, and remind them that sensation could vary depending on stimulation parameters.

Throughout the trial, participants will be requested to actively report adverse events (AEs), including but not limited to: skin irritation/erythema, dizziness, transient palpitations, or nausea potentially associated with taVNS; headache, scalp discomfort, tinnitus, or seizure-like episodes potentially associated with rTMS. Each reported AE will be documented in the participant’s case report form (CRF). In the event of a serious AE (SAE) deemed causally related to the intervention, the subject will be withdrawn from the trial and referred for appropriate medical care by the protocol-mandated SAE management algorithm.

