### Outcomes

The primary outcome is the MoCA-B score. Secondary outcomes include RBMT, MBI, P300 latency and amplitude. Any adverse events occurring during the intervention period, such as dizziness, pain, skin redness, and itchiness, will be reported by research assistants and managed by experienced physicians. We will assess the causality between adverse events and the treatment, as well as the severity of the adverse events. Serious adverse events will be reported to the ethics committee.

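### Participant self-report is the only described way of detecting adverse events in a cognitively impaired population, and the two AE passages disagree on source and time window

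*Protocol article*

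**What the plan says.** The Interventions section of the protocol article describes detection of adverse events, over the whole trial, as a request: "participants will be requested to actively report adverse events (AEs), including but not limited to: skin irritation/erythema, dizziness, transient palpitations, or nausea". It names four events for taVNS and four for rTMS, the latter being headache, scalp discomfort, tinnitus and seizure-like episodes. It then says "Each reported AE will be documented in the participant’s case report form (CRF").

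The Outcomes section describes the process differently. Its scope is "Any adverse events occurring during the intervention period, such as dizziness, pain, skin redness, and itchiness". Of these events it says only that they "will be reported by research assistants and managed by experienced physicians". Causality and severity are to be assessed, and serious events go to the ethics committee.

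On the population, the Introduction says of mild cognitive impairment: "It shows varying degrees of impairment in many cognitive areas such as memory, executive function, and language ability". Inclusion requires "A Clinical Dementia Rating (CDR) score of 0.5", and "Participants will be recruited from the clinic, inpatient ward, or long-term care facilities" near the study department. The Discussion gives evaluation of the combination's safety, alongside its effectiveness, as an aim.

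**The concern.** Self-report asks the participant to notice a symptom, keep it in mind and bring it up. Memory, executive function and language all bear on that, and these are the functions the Introduction says the condition impairs. Several of the named events (dizziness, palpitations, nausea, headache) are brief and leave nothing for staff to see later. A seizure-like episode is also poorly suited to the participant's own account.

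The Outcomes section does not close the gap. It says who passes the event on, not whether anyone asks. It also drops the follow-up period from the window, so a symptom between T1 and T2 is inside the AE definition in one section and outside it in the other.

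At stake is how the AE table can be read. The protocol presents this as the first combined use of the two devices in this condition, with 22 participants per arm. With so few, an absence of reported events says little about tolerability unless everyone was asked the same questions in the same way.

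**Working it through.** The protocol gives no AE rate, reporting probability or safety sample size, so there is no figure to reproduce. The text comes first, then an illustration on assumed values.

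**Comparison of the two sections**

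- Source: participants (Interventions); research assistants (Outcomes).
- Means of detection: a request to report (Interventions); none stated (Outcomes).
- Window: whole trial (Interventions); treatment period (Outcomes). Treatment lasts 4 weeks and T2 falls 4 weeks later, so the narrower window covers 4 of 8 weeks.
- Contacts: 5 days × 4 weeks = 20 sessions, so recall during treatment spans a day or a weekend. After T1 the text describes one further contact, T2, so recall can span 4 weeks.

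**Under-counting (p and s assumed)**

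Let n = 22 per arm (Sample size calculation), p = true risk of a symptom per participant, and s = probability that an affected participant's symptom is captured.

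Chance that an arm shows no case = (1 − p·s)^22. With p = 0.10:

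- s = 1: 0.90^22 = 0.098, or 10%.
- s = 0.5: 0.95^22 = 0.324, or 32%.
- Symptom recurring at three sessions, each reported independently with probability 0.5: s = 1 − 0.5^3 = 0.875, and (1 − 0.0875)^22 = 0.9125^22 = 0.13, or 13%.

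Expected counted cases = 22·p·s. With p = 0.30, 22 × 0.30 = 6.6 participants are affected; s = 0.9 counts 5.9 and s = 0.5 counts 3.3.

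**Unequal capture between arms (also assumed)**

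With equal true risk, the spurious risk ratio is s(active)/s(sham). The last column is the chance of a two-sided 5% difference at 44 v 44 (one device on v off) with p = 0.30.

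| s sham | s active | spurious ratio | chance of significance |
|---|---|---|---|
| 0.8 | 0.9 | 1.12 | 5% |
| 0.5 | 0.7 | 1.40 | 11% |
| 0.5 | 0.9 | 1.80 | 28% |

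A modest shift hardly shows. With p = 0.20 and s rising from 0.5 to 0.6, the observed rates are 0.20 × 0.50 = 10% and 0.20 × 0.60 = 12%. That is 2.20 v 2.64 of 22 participants, a gap of 0.44 of a participant. Better reporting under active treatment would make it look less safe, not safer.

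**The case against.** The strongest reply is that this is an article. It mentions a case report form and an SAE algorithm that are not shown, and the form may carry structured questions. A request that names specific symptoms can itself be read as prompting. Staff place the ear electrodes and the coil every weekday and could see redness or a seizure-like episode. Memory is only one of three domains that can qualify under Diagnostic criteria, CDR 0.5 is mild, and near-daily contact keeps recall short. Adverse events are also not listed among the primary or secondary outcomes.

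Much of this stands, and it limits the point. During treatment the loss may be small, as the 13% case shows, and it would be wrong to describe every participant as memory-impaired. It does not remove the point, because the article is not silent: it states a method, that method rests on the participant, and the section that might supplement it gives another window and no means of detection.

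A reader might go further and infer that AE rates will certainly be too low, or that capture will rise with memory improvement and so differ by arm. The documents support neither. They give no reporting rate, and nothing in them links AE reporting to the RBMT or the MoCA-B. Any memory gain would also build up over weeks, while events can occur from the first session.

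**Conclusion.** The point holds in a limited form. Participant self-report is the only detection route described, and Interventions and Outcomes disagree on source and window. Under-counting of transient symptoms is likely, chiefly in the 4 weeks after treatment, and nothing stated ensures that the four arms are asked alike. The size cannot be taken from the documents: the 10%, 32% and 13% figures rest entirely on an assumed 10% risk and assumed capture probabilities. Capture that depends on memory improvement is a possibility, not a finding. The primary efficacy analysis is unaffected; what is weakened is the safety evidence that the Discussion says the trial will provide.

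**What to change.** 1. Give Interventions and Outcomes one AE window, the whole trial to T2, and state how research assistants learn of events.
2. Keep self-report and add a yes/no checklist with fixed wording, covering all eight taVNS and rTMS events already listed under Interventions. Ask every participant in all four arms every item, whichever devices are active.
3. Ask it at each session (during this session and since the last), and again at T1 and T2. At T1 and T2 the blinded assessor should ask it, preferably after the cognitive tests are scored so that the answers cannot colour the scoring. Include a caregiver or facility informant where there is one.
4. Record solicited and spontaneously reported events separately, so that each can be tabulated by arm.

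The cost is about a minute per contact, at visits that already take place. More mild events will be counted in every arm, sham included. The session questions would be asked by staff who may know the allocation, since the blinding section confines blinding to assessors and statisticians; fixed wording limits that source of bias but does not remove it.
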